### Study treatments

The intervention of treatment lies in fluid management. To exclude the possible difference caused by different balanced crystalloid solution, acetate Ringer’s solution is chosen for balanced crystalloid infusion. After patient screening and grouping, participants will be assigned with acetate Ringer’s solution or saline for intravenous infusion accordingly. The volume, infusion rate, and additive content (e.g., potassium chloride) of the fluid will be determined by responsible clinicians. The intervention will last for 5 days after patients’ enrolment. Other solutions are permitted to be used as carrier fluids for the infusion of any drug on the occasion when neither acetate Ringer’s solution nor saline is considered compatible. Medication use except fluids will not be restricted in the study.

### Parallel control and allocation

Patients will be divided into 2 parallel groups: acetate Ringer’s solution versus saline. Crystalloids for enrolled patients are assigned according to the number of the month. Once assigned, the solution will be applied for the first 5 days during the patients’ stay in ICU. The assignment remains during change of month. The solution applied in the beginning month in each ICU is determined randomly by Excel2016 of Microsoft Office to make sure that stratified patient groups will be randomized to receive either acetate Ringer’s or saline solution, followed by a monthly rotation of fluids, so that any potentially observed difference in renal function is not due to other confounding factors such as use of nephrotoxic medication or contrast media. According to the Excel2016-generated random numbers, acetate Ringer’s solution will be applied in the odd month and saline will be applied in the even month both in the 2 centers. The random number table is operated by the primary investigator alone and clinicians are not involved in the process.

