### Study fluid distribution and logistics

Acetate Ringer's soution and saline administered in this trial both have different volume sizes of 250 ml and 500 ml. Components of these two crystalloids are presented (Table 2). The study is an open-label study; thus, the exact solution used is known to investigators, clinicians, and patients. Since the study is non-blind and two fluids used in this study have already been widely applied in the daily care of patients in the above ICUs, there are no problems of logistics.

**Table 2 Tab2:** Components of two crystalloids administered in the trial

Components (mmol/L)	Acetate Ringer’s solution	0.9% saline
Na	140	154
K	4	-
Mg	1	-
Ca	1.5	-
Cl	115	154
Glucose (%)	1	-
Buffer system	Acetate 25	-
Osmotic concentration (mOsmol/kg)	304	286

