### Statistical analysis

Measurement data that conform to normal distribution will be described as mean ± SD, while ones that do not will be reported as the median and interquartile range (IQR). Count data will be notified as frequencies and proportions. As for single-factor analysis, the difference of measurement data will be compared with *T* test between two groups or with one-way analysis of variance among three groups. Chi-square test and Fisher’s exact test will be used for rate comparison. As for multi-factor analysis, variables which showed a significant difference in the univariate analysis will be processed by logistic multivariate regression analysis. Multiple linear regression analysis will be used to demonstrate the linear relationship between variables. *P* value < 0.05 will be considered statistically significant. SPSS 24.0 will be used to complete data processing and statistical analysis.

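### Fluid follows one odd/even calendar rule in both ICUs: assignment is foreseeable, no month contains both fluids, and the simple tests, the logistic model and the sample size ignore the month

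*Protocol article*

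**What the plan says.** Under *Parallel control and allocation*, the unit of allocation is the month: "Crystalloids for enrolled patients are assigned according to the number of the month". The random element is the start: "The solution applied in the beginning month in each ICU is determined randomly by Excel2016 of Microsoft Office", after which fluids rotate monthly. The outcome is stated in full: acetate Ringer's solution "will be applied in the odd month and saline will be applied in the even month both in the 2 centers". A patient keeps the assigned fluid when the month turns. The section adds that "The random number table is operated by the primary investigator alone and clinicians are not involved in the process". It describes stratified groups of patients as randomised and says the rotation is used "so that any potentially observed difference in renal function is not due to other confounding factors".

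*Study fluid distribution and logistics* makes the trial open label: "the exact solution used is known to investigators, clinicians, and patients".

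*Statistical analysis* lists t tests and logistic regression, and says that chi-square and Fisher's "exact test will be used for rate comparison". *Additional secondary analysis* applies these methods to the secondary outcomes. *Main secondary analysis* uses a logistic model for the primary outcome. *Sample size and statistical power* makes no allowance for clustering. *Primary analysis* specifies a generalized linear mixed-effects model. Its listed fixed effects, which end in an open list, do not include month, ICU or period, and its random effects have no named grouping factor.

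**The concern.** Three consequences follow from a single calendar rule in both ICUs.

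- **No concurrent comparison.** In any month the whole trial starts new patients on one fluid. An outbreak, a staffing gap or a shift in case mix peculiar to that month falls entirely on that fluid. The second centre could have supplied a within-month contrast but, being in phase, supplies none.
- **No concealment.** After the first month the calendar gives every later assignment. Restricting access to the random number table hides nothing from unblinded staff who can read a date. Eligibility leaves some judgement, since infection need only be possible, so the decision whether or when to enrol can be influenced by the known fluid. Keeping the fluid after a month change protects patients already assigned, not that decision.
- **Patients treated as independent.** If outcomes are correlated within months, tests that ignore the month give standard errors that are too small.

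At stake is whether a difference, or its absence, can be attributed to the fluid. The article intends the result to inform guidelines.

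**Working it through.** **Inputs.** Recruitment runs from March 1, 2019 to February 28, 2022 in 2 ICUs (*Study sites and period*). N is 312, 156 per group (*Sample size and statistical power*). The article gives no intracluster correlation (ICC), so 0.01, 0.02 and 0.05 are assumed.

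**The plan's own figure.** With 35% in both groups, a margin of 1.5 points, one-sided 2.5% and 80% power, n per group = (1.960 + 0.842)² × 2 × 0.35 × 0.65 / 0.015² ≈ 15,873. So 312 is not reproduced from the stated inputs. That is a separate matter. Here 312 serves only as the planned number of patients.

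**Calendar pattern.** The period has 36 months, 18 odd (552 days) and 18 even (544 days). January, March, May, July, September and November are always Ringer's and the other six always saline, in both ICUs. Each named month occurs three times and never changes fluid, so the number of months with new enrolments to both fluids is 0.

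**What alternation does balance.** Numbering the months 1 to 36 from March 2019, Ringer's months are 1, 3, …, 35 (mean 18) and saline months 2, 4, …, 36 (mean 19). The mean dates differ by one month in three years, and each fluid samples the year at six evenly spaced months. Slow trend and smooth season are therefore roughly balanced. Effects specific to a month are not separable from fluid within that month.

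**Clustering.** With m patients per cluster, design effect DE = 1 + (m − 1) × ICC, effective N = 312 / DE, and the actual level of a nominal two-sided 5% patient-level test = 2 × [1 − Φ(1.96 / √DE)].

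- Month effects shared by both ICUs: m = 312 / 36 = 8.67.
- Effects within ICU-month: m = 312 / 72 = 4.33.

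| ICC | Shared month: DE | Effective N | Actual level | ICU-month: DE | Effective N | Actual level |
|---|---|---|---|---|---|---|
| 0.01 | 1.08 | 290 | 5.9% | 1.03 | 302 | 5.4% |
| 0.02 | 1.15 | 271 | 6.8% | 1.07 | 292 | 5.8% |
| 0.05 | 1.38 | 226 | 9.6% | 1.17 | 267 | 7.0% |

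**Sensitivity.** With 20% withdrawal (312 × 0.8 ≈ 250; m = 6.94), the shared-month levels are 5.7%, 6.4% and 8.5%. If each ICU ran only the 12-month minimum (24 ICU-months; m = 13), the ICU-month levels for 312 patients are 6.4%, 7.8% and 12.1%.

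**The case against.** The strongest reply has four parts.

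1. **The primary analysis may already handle the month.** It is a mixed model with random effects, and an article may leave the grouping factor to a full protocol or SAP. This stands. A reader might infer that all the trial's tests ignore the month. The documents do not support that for the primary model; they show only that it does not name month or ICU-month. The error rates above describe unadjusted patient-level tests, not that model.

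2. **Alternation protects against the obvious confounders.** This largely stands for slow trend and season, and the primary model also adjusts for severity, diagnosis, ventilation and vasopressors. A reader might infer gross seasonal confounding; the calendar arithmetic does not bear that out. But covariate adjustment does not create a within-month comparison or restore concealment, and it does not justify saying that rotation excludes confounding.

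3. **The in-phase pattern may be chance.** A reader might infer that one random draw fixed the whole trial. The article describes a random start in each ICU, so two draws that happened to agree fit the text equally well. The consequence for the comparison is the same. Nor does the article claim individual randomisation: it calls itself a parallel controlled trial and states assignment by month openly. The fault lies in the sentence about randomised groups and excluded confounding.

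4. **It is late to change the sequence.** This stands in part. The article appeared in January 2021, so from February 2021 at most 13 of 36 months can be altered and 23 stay in phase. The modelling and wording changes do not depend on this.

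**Conclusion.** The point holds in limited form. On the article's own text, assignment is foreseeable to unblinded enrolling staff throughout, and no month contains new enrolments to both fluids. The statement that rotation removes confounding is therefore not supported. These two design features carry the weight of the point. Foreseeable assignment is an opportunity for selection; nothing in the documents shows that selection has occurred.

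The analysis part holds for the t, chi-square and Fisher tests, the logistic model and the sample size. For the primary model it is only a request to name the random effects. Its size depends on assumed ICCs, equal recruitment per month and all 36 months in use. At an ICC of 0.01 the inflation is small (5.4% to 5.9%); at 0.05 it is 7.0% to 9.6%. The upper figure in each pair requires month effects fully shared by the two ICUs.

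**What to change.** 1. **Analysis.** In the primary model and every between-fluid secondary comparison, include ICU as a fixed effect (two centres cannot support a random effect), a smooth calendar-time term, and random effects for calendar month and ICU-month. The calendar-month term is needed for the months run in phase, because ICU-month alone misses an effect shared by both ICUs. Use these models in place of unadjusted t, chi-square, Fisher and ordinary logistic tests for inference between fluids.
2. **Sequence.** For the recruitment months that remain, reverse the order in one ICU so that both fluids are in use each month. *Study sites and period* requires equal months per fluid in each ICU, so make the change after an even number of completed months there. That ICU then has two consecutive months of one fluid at the changeover. Months already run stay in phase.
3. **Enrolment.** Tie assignment to the month of ICU admission, since the article does not say which date governs, and enrol consecutive eligible patients.
4. **Description.** Call the design cluster-period alternation with a random start, and delete the claim that the rotation excludes confounding.

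**Cost.** Slightly wider confidence intervals and a short amendment through both ethics committees. Both fluids are already in routine use in both ICUs, and the article reports no logistic obstacle. If recruitment has closed, items 1 and 4 still apply, and the lack of concealment has to be reported as a limitation.

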### Study fluid distribution and logistics

Acetate Ringer's soution and saline administered in this trial both have different volume sizes of 250 ml and 500 ml. Components of these two crystalloids are presented (Table 2). The study is an open-label study; thus, the exact solution used is known to investigators, clinicians, and patients. Since the study is non-blind and two fluids used in this study have already been widely applied in the daily care of patients in the above ICUs, there are no problems of logistics.

**Table 2 Tab2:** Components of two crystalloids administered in the trial

Components (mmol/L)	Acetate Ringer’s solution	0.9% saline
Na	140	154
K	4	-
Mg	1	-
Ca	1.5	-
Cl	115	154
Glucose (%)	1	-
Buffer system	Acetate 25	-
Osmotic concentration (mOsmol/kg)	304	286

### Study outcomes

The primary outcome is MAKE28 (major adverse kidney events) [22]—a composite of in-hospital death, new renal replacement therapy, or persistent renal dysfunction (defined by an estimate glomerular filtration rate (eGFR) lower than 60 ml/min/1.73 m^2^ for at least 3 months [23, 24]) within 28 observational days.

Secondary outcomes will include:
The occurance of AKI which is diagnosed according to the Kidney Disease Improving Global Outcomes (KDIGO) criteria [25];Twenty-eight day mortality;Electrolyte disturbance, including hypernatremia, hyperchloremia, and hyperkalemia as well as hyponatremia, hypochloremia, and hypokalemia;Changes of renal functions based on the biomarkers measured from the participants’ plasma and urine samples collected in the first 3 days after enrolment; andOther clinical outcomes: ICU stay days, ventilator days, vasopressor days, and RRT days.

Pre-specified subgroups for primary and secondary outcome analyses will mainly include:
With or without acute kidney injury (no AKI, AKI stage 1, AKI stage 2, or AKI stage 3);With or without septic shock;Low versus high severity of sepsis: mild, moderate, and severe (classified by SOFA scores or Acute Physiology and Chronic Health Evaluation II (APACHE II) scores); andIntravenous infused volumes of the assigned crystalloids.

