**Methods/design:**

The investigators designed a pragmatic, multi-center parallel controlled trial recruiting 312 patients who are diagnosed with sepsis/septic shock in the intensive care unit (ICU) and will be assigned with either acetate Ringer’s solution or saline in the corresponding month. Patients with an end-stage renal disease (ESRD) or who need renal replacement therapy (RRT) prior to or at the time of enrolment are excluded. Enrolled patients will be regarded as with mild, moderate, or severe sepsis on the basis of the severity of their illness and will be divided into subgroups according to their initial renal function and various intravenous infusion volumes when being analyzed. The primary outcome is major adverse kidney events within 28 days (MAKE28), including the composite of in-hospital death, receipt of new renal replacement therapy, or persistent renal dysfunction. Secondary outcomes include 28-day mortality, internal environment disturbance, incidence and duration of vasoactive drug treatment, duration of mechanical ventilation, duration of RRT, and ICU and hospital length of stay.

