Until now, the choice of crystalloid for critically ill patients has not been confirmed [15, 16]. The SPLIT (Saline v Plasma-Lyte 148 for Intensive Care Unit Fluid Therapy) study conducted in four New Zealand ICUs [15] concluded with no difference neither in the primary outcome of the incidence of AKI nor in secondary outcomes of RRT use and mortality between the use of a buffered crystalloid and saline. However, this study was criticized for the relatively small volume of fluid as it may have been too low to cause detectable renal toxicity [16]. Another trial comparing saline to buffered crystalloid solutions (lactated Ringer’s solution and Plasma-Lyte A) in a single ICU, the SALT (Isotonic Solution Administration Logistical Testing) study, demonstrated no difference in the overall incidence of AKI or major adverse kidney events (MAKE30) including death from any cause, new receipt of renal replacement therapy (RRT), or persistent renal dysfunction within 30 observational days. However, notably, there was a difference on MAKE30 in septic patients who received larger volume of crystalloids in subgroup analysis. The study showed a dose-response relationship [16]. A recent multiple-crossover trial in critically ill adults in 5 ICUs demonstrated that the use of balanced crystalloids resulted in a lower rate of MAKE30 than the use of saline [17] though it showed no significant difference in the incidence of AKI and mortality respectively. It also showed difference in the sepsis subgroup, but the potential dose-response relationship related with infusion volumes in the subgroup was not clarified [18]. Both of the 2 studies implied that it is necessary to investigate further in septic patients as they are more prone to fluid damage. It still remains uncertain whether balanced crystalloid is superior than saline in septic patients, whether it is related to their initial renal function, and whether there is a dose-response relationship between fluids and outcomes. Thus, we carry out this study for further investigations.

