**Fig. 1 Fig1:**
[figure not shown]
Standard Protocol Items: Recommendations for Interventional Trials (SPIRIT) checklist. Baseline variables include baseline renal function, main diagnosis and complications, severity of illness at enrolment, demographic characters, and admission location. Intravenous fluid includes saline, acetate Ringer’s solution, and other fluids. Receipt of invasive support includes mechanical ventilation, receipt of RRT, and vasopressors. Clinical outcomes include vital status, vasopressor days, mechanical ventilation days, RRT days, ICU stay days, hospital length of stay and serum creatinine at hospital discharge

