### Sample size and statistical power

The sample size was calculated based on the occurrence of MAKE30 on septic patients, which was around 35% [17]. With a noninferiority limit of 1.5%, a total of 312 study participants (156 in each group) would result in a power of at least 80% with a one-sided type-1 error rate (*α*) of 2.5%, allowing a 20% withdrawal rate in each group.

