### Additional secondary analysis

Statistical methods mentioned in the statistical analysis will be applied according to the characteristics and distribution of the data.
Compare the secondary outcome between the two groups;Subgroup analysis will include:
Septic shock (yes/no)Stage of AKI on the enrolment day (no AKI, AKI, chronic kidney disease without receiving RRT regularly)intravenous volumes of the assigned crystalloidsThe APACHE II scores and SOFA scores at the day of enrolmentReceipt of mechanical ventilation (yes/no) and ventilation daysReceipt of vasopressor (yes/no), vasopressor category, and max dosesReceipt of RRT (yes/no) and RRT daysMain diagnosis at the time of admission to hospital (nervou s system disease, respiratory system disease, cardiovascular system disease, digestive system disease, urinary system disease, hematologic system disease, endocrine system disease)Complications (hypertension, diabetes, coronary heart disease, etc.)

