### Data collection and management

Patients’ demographic data, main diagnosis, comorbidities, assigned crystalloids, general vital signs, SOFA scores, APACHE II, infection indices, and indices of multi-organ function including renal function, respiratory function, cardiac function, etc. at the time of enrolment will be collected as baseline data. Clinical information including infection indices (white blood cell count, procalcitonin, etc.), organ function indices (renal function (creatinine, urea nitrogen, cystatin C, urine volumes, etc.), respiratory function (PO_2_/FiO_2_, ventilation situation, etc.), hepatic function (total bilirubin, etc.), and indices of internal environment (blood gas analysis) will be detected during the first 5 days in ICU, and treatments such as vasopressors, mechanical ventilation, RRT, and electrolyte supplement will be recorded. These data and infused volumes of the assigned fluids will be collected for at least 5 days or until ICU discharge. ICU stay days, vasopressor days, RRT days, and ventilation days will be counted during 28 days after enrolment. These data will be collected to assess and analyze primary and secondary outcomes. Besides, patients’ blood and urine samples within the first 3 days after enrolment will be collected and stored for testing possible biomarkers for identifying AKI at an early stage.

Patients’ information and clinical data will be collected from the Hospital Information System (HIS) of the hospitals involved in this study and recorded in the Case Report Format (CRF) by the trial manager or trained personnel. An electronic password-protected excel, which will be applied for statistical analysis, will be created to summarize the data of all participants. All the data will be accessed by only investigators and authorized personnel to monitor the completeness and authenticity of the table. The confidentiality is secured and all the data will be preserved for the purpose of a secondary analysis or investigations by the investigators. To protect patients’ privacy, their names will not appear on the CRF table. Every participant will only be recognized by their study ID.

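### The renal component of MAKE28 demands 3 months of low eGFR inside a 28-day window, so no kidney dysfunction that starts at or after enrolment can count

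*Protocol article*

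**What the plan says.** The Study outcomes section makes MAKE28 "a composite of in-hospital death, new renal replacement therapy, or persistent renal dysfunction", and defines the last of these as an eGFR below 60 ml/min/1.73 m² "for at least 3 months [23, 24]) within 28 observational days". The word new is attached to RRT only, and the eGFR criterion has no reference to the patient's own baseline.

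Four other places bear on how the component could be scored:

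- **Follow-up.** The Fig. 1 caption lists, among the clinical outcomes, "hospital length of stay and serum creatinine at hospital discharge". Under Data collection and management, days in the ICU and on vasopressors, RRT and ventilation "will be counted during 28 days after enrolment". No assessment at 3 months is described.
- **Missing data.** Under Handling of missing data, a survivor without new RRT who has no creatinine value from enrolment to hospital discharge is scored as free of MAKE.
- **Eligibility.** The exclusions cover RRT, a single kidney, transplant and named causes of AKI, and the abstract adds end-stage disease. Chronic kidney disease short of that is not excluded, and Additional secondary analysis plans a category for "chronic kidney disease without receiving RRT regularly".
- **Planning rate.** The Sample size section opens: "The sample size was calculated based on the occurrence of MAKE30 on septic patients, which was around 35% [17".

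**The concern.** The duration and the window contradict each other within one sentence of the primary endpoint. The trial asks whether saline harms the kidney in sepsis, and whether this depends on initial renal function and volume infused. Persistent dysfunction is the only part of the composite that can register kidney injury in a patient who survives without dialysis. If it cannot register a new case, the primary outcome is in effect death or new RRT, possibly with a baseline trait added.

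The practical risk is improvisation. Whoever scores the outcome has to replace the rule with something workable. The trial is open-label and already recruiting, so a rule chosen late could be chosen with results by arm in view.

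**Working it through.** The plan gives no figure for this component. Its only event rate is 35% for a whole composite, with no split by component, so there is nothing to reproduce. The sample size arithmetic is a separate matter and is not used here.

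**Inputs**

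- Required duration: at least 3 months (Study outcomes). Assumed to be 90 days; calendar months give 89 to 92.
- Window: 28 days from enrolment (Study outcomes).

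**Step 1: can a new case qualify?** If eGFR first falls below 60 on the day of enrolment, its longest observable duration is 28 days.

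- Share of the required time: 28 / 90 = 31%.
- Shortfall: 90 − 28 = 62 days (61 with 89 days, 64 with 92).

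Later onset only widens the gap. New qualifying cases: zero.

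**Step 2: who could qualify literally?** The low eGFR must have begun at least 90 − 28 = 62 days before enrolment (61 to 64), and must then persist to day 28. A fall caused by the present septic episode a few days before ICU admission also fails. What remains is long-standing low eGFR, and the criteria do not exclude such patients unless they have end-stage disease or meet one of the listed renal exclusions.

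**Step 3: what would each literal reading do?**

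- If long-standing low eGFR is not regarded as an event within the window, the component is empty and MAKE28 is death or new RRT.
- If it is counted, those patients are events whatever fluid they receive. Let c be their share, equal in both arms. The difference between arms in the composite is then (1 − c) × the difference among the other patients. This pulls the arms together, which matters because the sample size is framed as noninferiority. The documents give no value for c.

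**Step 4: does other text repair the definition?** Onset by day 28 with confirmation at 3 months would need follow-up that is not described. The missing-data rule points the other way: it presumes that a creatinine between enrolment and discharge decides the component. It supplies no threshold, so it shows the intention without providing a usable rule.

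**The case against.** The strongest reply is that the investigators plainly meant an in-hospital assessment. The missing-data rule and the discharge creatinine both show this, so the literal 3-month rule would probably never be applied. That stands as evidence of intent. It does not settle the endpoint, because no other text gives a cutoff, and an analysis plan that supplied one would depart from the published primary outcome.

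Three stronger readings go beyond the documents:

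- **That pre-existing kidney disease will be scored as an event.** A reader might infer this from the lack of a baseline reference. The protocol never says it, and an event within 28 days can equally be read to exclude a long-standing condition. A reader might also put a size on it from an assumed prevalence of kidney disease and an assumed rate of death or RRT. The article gives neither, so any such percentage would only restate the assumptions.
- **That the 35% is known to come from a different definition.** The Background speaks of death, new RRT "or persistent renal dysfunction within 30 observational days", but that sentence describes the single-ICU SALT study. The 35% is cited to the later multiple-crossover trial, whose renal definition the article does not give. The gap between 30 and 28 days is trivial; only the 3-month clause could create a real mismatch. What can be said is that the rate has not been shown to apply.
- **That an absolute eGFR threshold is itself an error.** It is a legitimate choice. The defect is the duration, together with silence on how prior low eGFR is scored.

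The article is condensed and its schedule and flow figures are not shown, so the fair statement is that no 3-month assessment is described, not that none exists.

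**Conclusion.** The point holds for the renal component. As written, it can record no dysfunction that starts at or after enrolment: 28 days of follow-up against about 90 required. This rests only on the wording of Study outcomes and on taking 3 months as 89 to 92 days. Read literally, the component is either empty or limited to patients with about 62 days or more of prior low eGFR.

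This is a stated rule that cannot work, not a detail left to a fuller document, and it concerns one of three components of the primary outcome. It needs correcting before the outcome is analysed. The consequence for the event rate, the treatment difference and power cannot be computed, because the article gives neither component rates nor the frequency of prior kidney disease.

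**What to change.** Amend the definition in Study outcomes as follows:

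1. Delete the 3-month duration. Judge the component on the last serum creatinine or eGFR at or before hospital discharge or day 28, whichever comes first, among survivors without new RRT. This agrees with the existing missing-data rule.
2. State one threshold.
3. State how patients with low eGFR before the illness are scored, so that unchanged prior kidney disease is not an event.
4. If the threshold is relative to baseline, name a pre-illness value where one exists and a fallback where it does not. The first creatinine after enrolment, which Main secondary analysis uses for initial renal function, may already be raised by septic AKI. With that value as baseline, unresolved injury at discharge could be scored as no event.
5. Check that the 35% planning rate refers to the same definition, and say so in the Sample size section.
6. Fix all of this before any comparison by arm.

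The cost is a protocol and registry amendment. Creatinine at discharge is already collected. For patients still in hospital on day 28, the last value up to that day would have to be taken from the hospital information system. The article does not say that pre-illness creatinine values are collected, so they would have to be retrieved where they exist.
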